**Clinical mediators**					
	Behavioral activation			BADS-SF^a^ [58]	
	Pain acceptance			CPAQ-8^b^ [59,60]	
	Sleep difficulty			AIS^c^ [61]	
**Outcomes**					
	**Engagement (proximal)**				
		Immediate engagement^d^ (primary outcome)		See Table 2 for JITAI^e^-specific definitions	
		Engagement need^d^		Number of times that the decision rule criteria were met to trigger each JITAI	
		**Engagement dose**			
			Touches	Number of times a user interacted with Wysa for Chronic Pain (eg, opened a notification, navigated through the app, sent a message to the chatbot, etc)	
			Sessions started	Number of times a digital tool session was opened (even if not completed)	
			Sessions completed	Number of times a digital tool session was completed	
		Retention		Number of days from onboarding until the last day of engagement with Wysa for Chronic Pain	
		Engagement content		Number of interactions in which the participant engaged with each of the following tool types: digital cognitive behavioral therapy tools, digital mindfulness and meditation tools, and digital sleep tools	
	**Clinical (distal)**				
		Depressive and anxiety symptoms^f^ (primary outcome)		PHQ-ADS^g^ [56,57] (Combination of PHQ-9^h^ and GAD-7^i^)	
		Disability		WHODAS 2.0^j^	
		Quality of life		Global QOL^k^ [62]	
		Pain interference		BPI^l^, Pain Interference domain [63]	

^a^BADS-SF: Behavioral Activation for Depression Scale-Short Form.

^b^CPAQ-8: Chronic Pain Acceptance Questionnaire-8.

^c^AIS: Athens Insomnia Scale.

^d^These measures will have unique values for each just-in-time adaptive intervention tested. Values for all other measures will be the same across all JITAIs tested.

^e^JITAI: just-in-time adaptive intervention.

^f^PHQ-9 and GAD-7 scores will also be reported separately [47,48].

^g^PHQ-ADS: Patient Health Questionnaire Anxiety and Depression Scale.

^h^PHQ-9: Patient Health Questionnaire-9.

^i^GAD-7: Generalized Anxiety Disorder-7.

^j^WHODAS 2.0: World Health Organization Disability Assessment Schedule 2.0.

^k^Global QOL: Global Quality of Life Scale.

^l^BPI: Brief Pain Inventory.

The primary end point for each MRT will be 12 weeks, which is a common end point for digital mental health trials to assess durability (Table 4) [6]. Because engagement is known to rapidly wane with digital interventions (and to facilitate mediation analyses), patient-reported measures will also be assessed at 4 and 8 weeks.

**Table 4 table4:** Timing of data collection for each microrandomized trial.

Measure			Baseline		Week 4		Week 8		Week 12^a^
Participant characteristics			✓						
Clinical mediators			✓		✓		✓		✓
**Outcomes**									
	Engagement (proximal)			✓		✓		✓	
	Clinical (distal)	✓		✓		✓		✓	

^a^Primary end point.

### Data Collection and Management

#### Qualitative Interviews

Qualitative feedback will be obtained from a subgroup of approximately 5-10 trial participants through semistructured interviews after each trial. Participants will be asked to share perceptions of the strengths, limitations, and suggestions for improvement related to the JITAIs. Participants will be purposively sampled to represent a range of sociodemographic characteristics and engagement patterns. The interviews will occur through secure audio and video recording hosted by a HIPAA (Health Insurance Portability and Accountability Act)–compliant Zoom (Zoom Communications, Inc) platform. Recording files will be stored on the study institution’s encrypted cloud server, Box (Box, Inc).

#### Retention Strategies

To improve retention, participants will be asked to complete the baseline study questionnaires immediately after the recruitment and enrollment process [64]. They will receive electronic gift cards for each time point that they complete all study questionnaires, but participants will not be paid for their level of engagement with the intervention since this is an outcome of interest. Rather, engagement will be monitored for all participants, regardless of whether they complete study questionnaires through the final study time point. A study team member will reach out to a trial participant by phone call, SMS text message, or email for reminders as needed if the participant does not complete electronic study questionnaires despite repeated automated prompts.

### Statistical Methods

#### Primary Outcome

The main purpose of the initial 4-week pilot trial is to determine the initial randomization probability for each JITAI in the first MRT for the “Wysa for Chronic Pain with JITAIs” intervention arm (ie, to construct a robust informative prior, also called a warm start, for each JITAI). We will also perform between-group comparisons of the primary proximal outcome for each JITAI between the intervention versus control arm (ie, comparison of the primary engagement outcome during the target engagement time interval between participants in the intervention arm when they met prespecified criteria and received JITAIs vs participants in the control arm when they met the same prespecified criteria but did not receive JITAIs). In the subsequent MRTs, analysis of the primary proximal outcome for each JITAI will account for both between-group and within-participant comparisons because participants in the “Wysa for Chronic Pain with JITAIs” arm may have met the prespecified criteria for any given JITAI multiple times during the study period. A secondary analysis of each MRT will also be performed to again construct a prior (warm start) for the subsequent MRT, for instance, centered at the estimated optimal JITAI strategy.

#### Interim Analyses

Interim analyses will be performed to ensure the specified randomization probabilities are producing a sufficient frequency of JITAI delivery to facilitate analysis of the primary outcomes, and randomization probabilities may be updated as needed throughout the trials. No interim analyses of the study outcomes will be performed. Given the relatively short duration and low risk of each trial, early stopping of a trial will only be considered if the data safety monitoring board (DSMB) determines that the intervention is contributing to one or more serious adverse events (SAEs), and the risks of continuation of the study outweigh the potential benefits to the enrolled participants. This is because the risk of harm from the intervention is low, and all participants will be receiving the same established therapeutic content. Sustained engagement and treatment effects are important secondary analyses, and early cessation of trials would jeopardize these analyses.

#### Additional Analyses

In a secondary analysis, we will evaluate whether the JITAIs’ effects on engagement vary with time based on the week of the study. The distal clinical outcomes in Table 3 at weeks 4, 8, and 12 will be analyzed using mixed-effects models to test for moderating effects of participant characteristics—for example, age group (middle-aged: 45-64 years vs older adult: 65 years or older), sex, race and ethnicity, depression or anxiety severity [6], and chronic pain duration—and engagement with the Wysa app (ie, total dose, duration, and content) by including these as interaction terms.

We will also estimate optimal JITAIs for the distal clinical outcomes using methods from reinforcement learning [65,66], and we will evaluate the appropriateness of engagement as a surrogate for long-term clinical outcomes by comparing the performance of an optimal JITAI that targets engagement with one that is optimized for the distal clinical outcomes of interest.

Other secondary analyses will include development of models that predict the likelihood that a user will disengage with Wysa for Chronic Pain; descriptive analyses of the estimated optimal JITAI (eg, if, when, and for whom a JITAI should be recommended); and testing for heterogeneity across patients (ie, comparing the performance of a JITAI rule developed from data pooled across all participants to the performance of a rule learned from each participant’s individual trajectory of data).

Our experimental therapeutics model will be assessed by evaluating for associations between engagement with tools related to each therapeutic target (ie, behavioral activation, pain acceptance, and sleep quality), patient-reported improvement in the corresponding target (ie, clinical mediators), and subsequent improvement in distal clinical outcomes. We will also investigate whether and how these associations vary across patient characteristics, such as age, depression or anxiety severity, pain interference severity, and self-reported digital savviness.

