**Methods:**

Using a mixed methods, human-centered design approach and a series of randomized trials, we will test and iteratively refine just-in-time adaptive interventions (JITAIs) that are designed to increase engagement with a digital mental health intervention. Participants will be aged 45 years or older, endorse at least moderately severe depression or anxiety symptoms (Patient Health Questionnaire-9 or Generalized Anxiety Disorder-7 score ≥10), and have coexisting chronic pain (ie, pain on most days or every day in the past 3 months), and live in the United States. In this open, web-based trial, participants will all receive Wysa for Chronic Pain (by Wysa), which uses a behavioral activation framework and encourages users to work toward pain acceptance. The fully automated intervention also includes cognitive behavioral therapy, mindfulness, and sleep tools, among others. In each trial, participants will be randomized during a maximum 12-week study period to receive versus not receive novel JITAIs that are intended to reduce navigation burden and improve usability (and subsequent engagement and clinical effectiveness). The JITAIs are being designed with iterative user feedback, guided by the Discover, Design/Build, and Test framework and the Behavioral Intervention Technology model. The proximal outcome for each JITAI is related to engagement with Wysa for Chronic Pain after JITAI delivery (compared to when no JITAI is delivered). The primary distal clinical outcome is the Patient Health Questionnaire Anxiety and Depression Scale. Based on statistical analysis that is triangulated with qualitative feedback from a subsample of trial participants, the JITAIs will be iteratively refined and retested in subsequent microrandomized trials until retesting of refined adaptations no longer yields meaningful improvement in immediate engagement or a maximum of 5 total trials have been completed.

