### Goal of This Study

We are conducting a large-scale, 3-phase project using human-centered design and the Discover, Design/Build, and Test (DDBT) framework to optimize an existing digital mental health intervention (Wysa for Chronic Pain) for middle-aged and older adults with depression or anxiety and coexisting chronic pain [43]. In the first project phase, we conducted semistructured interviews and usability testing among this target user population. During that process, novel JITAIs for Wysa for Chronic Pain were developed using the Behavioral Intervention Technology (BIT) model [36,44], which links established behavior change strategies with technology-related design and implementation factors—for example, timing, medium (text, audio, or video), and complexity of intervention delivery—that affect engagement and subsequent effectiveness of a digital health intervention [44,45].

This study protocol outlines the second project phase. In a series of traditional and microrandomized trials (MRTs) that are interspersed with qualitative feedback from a subgroup of trial participants, the goal of this study is to test and optimize the effectiveness of the novel JITAIs to increase engagement among middle-aged and older adults with Wysa for Chronic Pain. The central hypothesis is that incorporating these JITAIs will increase engagement with Wysa for Chronic Pain by improving usability and, subsequently, will improve depression and anxiety symptoms in this population. After completion of this phase, the third project phase will be a pragmatic, hybrid type 1 effectiveness-implementation trial during which the final JITAIs will be fully integrated into the Wysa for Chronic Pain user experience.

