#### Sample Size

Sample size calculations were performed at a 5% significance level to detect an effect in the primary study outcome between the 2 study arms. Because the primary outcome for each JITAI is related to engagement (which is automatically captured by the Wysa platform and does not require participant report), we assumed a 10% attrition rate (conservatively assessed as occurring at baseline but after downloading Wysa for Chronic Pain). In the initial 4-week pilot trial, we will enroll 29 participants into each of the 2 arms (58 participants total). This will provide 80% power to detect a large effect size (Cohen *d*=0.8).

Sample size determinations for the subsequent 12-week MRTs will be dependent on analysis after each preceding trial, but it is anticipated that control groups for analysis will be pooled by including the control groups from previous trials. For the first MRT, we preliminarily anticipate enrolling 75 participants into the “Wysa for Chronic Pain with JITAIs” intervention arm and 46 participants into the “Wysa for Chronic Pain without JITAIs” control arm (121 total participants recruited). In the intervention arm, clipped Thompson sampling will be used to make intervention assignments with the clipping rate set at 10%. This would provide 80% power to detect a moderate to large effect size (Cohen *d*=0.5). For the second MRT, we preliminarily anticipate enrolling 120 participants into the intervention arm and 55 participants into the control arm (175 total participants recruited). Clipped Thompson sampling will again be used in the intervention arm, with a 10% clipping rate. This would provide 80% power to detect a moderate to small effect size (Cohen *d*=0.4). Sample sizes for any additional MRTs will follow a similar calculation process.

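### Age is cut at 65 for the moderation test; if moderation is roughly linear in age, this costs about a quarter to a half of the age information, and continuous age would be the better primary test

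*Protocol article*

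**What the plan says.** Under Additional Analyses, the distal clinical outcomes at weeks 4, 8 and 12 are to be analysed with "mixed-effects models to test for moderating effects of participant characteristics", with the moderators entered as interaction terms. Age is one of several moderators given as examples. It is the only participant characteristic in that list with numerical cut points: "age group (middle-aged: 45-64 years vs older adult: 65 years or older". No reason is given for cutting age inside the model, and no continuous-age analysis of the distal outcomes is mentioned.

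Later in the same section, the analysis of therapeutic targets asks whether associations vary across characteristics "such as age, depression or anxiety severity, pain interference severity, and self-reported digital savviness". There age carries no cut.

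The abstract's Methods set the age range as "aged 45 years or older", and Textbox 1 adds no upper limit. The age distribution is not described. Goal of This Study names the target population as "middle-aged and older adults with depression or anxiety and coexisting chronic pain". Sample Size gives totals of 58 (pilot), 121 (first MRT) and 175 (second MRT). All are sized for a difference between arms, not for an interaction.

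**The concern.** A two-level age term estimates one contrast between two averages and ignores variation in age within each group. The protocol's own case for age, in the Background, rests on vision, dexterity, cognition and how often people check their phones. It describes age-related change and names no threshold at 65. If moderation follows such a gradient, the cut discards usable information.

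Interaction tests are already weak at these sample sizes. A further loss makes it more likely that a finding of no difference by age is a missed difference. In a project that adapts an app for middle-aged and older users, such a null could be taken as support for one design across the whole age range.

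**Working it through.** **1. The plan's own figure.** No power or sample size is stated for the moderation test, so the nearest stated figure is the pilot's. Inputs from Sample Size: "Sample size calculations were performed at a 5% significance level" (taken as two-sided), 80% power, d = 0.8, and "we assumed a 10% attrition rate". A two-sample t-test needs 26 per arm, and 26 / 0.90 = 28.9, rounded up to 29. This reproduces "29 participants into each of the 2 arms (58 participants total".

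**2. Share of linear age information kept by a cut.** This is the squared correlation between age and the indicator for 65 or older. Let p be the share aged 65 or older; p is an assumption.

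- Normal ages: φ(z)² / [p(1−p)], where z is the normal quantile at 1−p.
- Uniform ages: 3p(1−p).

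Power after the cut, for a test with 80% power on continuous age, is Φ(2.80 × √share − 1.96), where 2.80 = 1.96 + 0.84.

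| p | Age shape | Share kept | Power after cut |
|---|---|---|---|
| 0.50 | uniform (45-85) | 3 × 0.5 × 0.5 = 0.75 | Φ(0.465) = 68% |
| 0.50 | normal | 0.399² / 0.25 = 0.64 | Φ(0.28) = 61% |
| 0.20 | normal | 0.280² / 0.16 = 0.49 | Φ(0.00) = 50% |
| 0.20 | uniform (45-70) | 3 × 0.2 × 0.8 = 0.48 | Φ(−0.02) = 49% |

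Over p = 0.20 to 0.50, the share kept is therefore 48-75% and the power 49-68%.

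**3. Sensitivity to the age distribution.** The normal formula ignores the age floor of 45. Simulated normal ages truncated to 45-90 (SD 10 before truncation) keep 57% with 19% aged 65+, 64% with 33%, and 66% with 51%, all inside the range above. The range is not a bound: with 10% aged 65+, the normal formula keeps 34%.

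**4. Sensitivity to the shape.** The squared correlation is symmetric. If the effect is a step at 65, the indicator keeps everything and a linear age term keeps only 48-75%.

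**5. Equivalent sample size.** Before attrition and before any pooling of controls:

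- First MRT: 121 × 0.75 = 91, down to 121 × 0.48 = 58.
- Second MRT: 175 × 0.75 = 131, down to 175 × 0.48 = 84.

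**6. How strong the two-level test is.** Assume an age-group-by-arm interaction, each trial's own controls, 10% attrition and a single time point. With n₁ and n₀ the retained arm sizes, the standard error in SD units is √{[1/(p(1−p))] × (1/n₁ + 1/n₀)}. The difference detectable with 80% power is 2.80 times that.

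- First MRT, n₁ = 67.5 and n₀ = 41.4: 2.80 × √(4/67.5 + 4/41.4) = 1.1 at p = 0.5, and 2.80 × √(6.25/67.5 + 6.25/41.4) = 1.4 at p = 0.2.
- Second MRT, n₁ = 108 and n₀ = 49.5: 0.96 and 1.2 in the same way.

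**The case against.** **The cut has a purpose.** A reader might infer that it brings no gain at all. The documents do not support that. Middle-aged and older adults are the protocol's two named target populations, the Background gives separate chronic pain prevalences for them (26% and 31%), and the cut is prespecified with those labels. A contrast between them answers a question the protocol poses. This stands, and it is a reason to keep the contrast in the report. It does not require the two-level term to be the only test.

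**The size of the loss is conditional.** A reader might take a quarter to a half as a property of the plan. It is not: it follows from an assumed share aged 65+ and from linear moderation. This stands in full.

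**The test is weak either way.** Suppose an interaction of 0.4 SD in the first MRT with an even split. The standard error is 0.395, so power is Φ(0.4/0.395 − 1.96) = 17%. With continuous age, and the cut keeping 64%, it is Φ(1.01/0.80 − 1.96), about 25%. A null would say little in either case. This limits the benefit, but the more efficient test still costs almost nothing and also gives narrower intervals under linear moderation.

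**The relevant trials are not all of them.** A reader might apply the loss to every trial from 58 to 175 participants. The pilot lasts 4 weeks and cannot supply weeks 8 and 12. Planned pooling of earlier controls would raise the analysed numbers above the MRT totals. Both stand.

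**Little rests on it.** Age is an example in a secondary analysis, and it appears uncut later in the same section. A fuller plan, not shown, may add functional forms. This keeps the grade low. The cut itself is nonetheless stated in the text and is not simply left open.

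**Conclusion.** The point holds as a minor improvement. The protocol puts age into the distal-outcome interaction as a two-level group, and its own rationale suggests graded change more than a step. Given linear moderation and 20-50% of participants aged 65+, the cut keeps about 48-75% of the age information and turns 80% power into about 49-68%. Fewer older participants would make the loss larger; a true step at 65 would reverse the ranking.

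The 80% is a yardstick for comparison, because the protocol claims no power for interactions. No sample size, primary outcome or primary conclusion depends on this choice. The use of age in two forms within one section is not a contradiction, since the two analyses differ, but it shows that uncut age is compatible with the plan.

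**What to change.** In Additional Analyses, state that age moderation of the distal outcomes is tested with age as a continuous variable: a linear interaction as the test, and a spline as a check on its form. Report model-based effects at a few ages chosen in advance, together with the 45-64 versus 65+ contrast for the two named populations. Settle this before the MRT outcome data are analysed, so that the form of age is not chosen after seeing results.

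The cost is wording, with no added participants, visits or questionnaires. It assumes that age is held in years; the article does not say so, and this should be confirmed. The small downside is that linearity is itself an assumption, which the spline and the group contrast are there to check.

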#### Missing Data

Once randomized participants download the Wysa for Chronic Pain app and initiate onboarding, proximal engagement outcomes will be automatically collected by the Wysa platform, regardless of how much or even whether a participant engages with Wysa for Chronic Pain during the rest of the study period, so these data points are not expected to be missing. For participant-reported questionnaire data, all questions will be designed as “required,” but participants will have the option to select “prefer not to answer” for sensitive descriptive variables. In these situations, “prefer not to answer” will be treated as a distinct covariate category in the analyses (rather than as missing data) since it will not necessarily be selected at random and may represent a distinct subgroup of participants. Multiple imputation for sequential randomized trials will be used to address missing data, for instance, if a participant does not complete questionnaires at a follow-up time point or withdraws from the study [67].

### Qualitative Analysis

Recordings of participants’ interviews will be professionally transcribed. A hybrid inductive-deductive coding approach will be used, with the BIT model as a framework. At least 2 team members will be involved in thematic analysis. The primary goal of the qualitative analysis is to identify opportunities for refinement of the JITAIs (eg, decision rules, intervention options, intervention language, etc) to improve their usability and effectiveness.

### Data Sharing Plans

Deidentified participant-level data will be shared through the NIMH Data Archive. Access to the dataset will be managed by the NIMH Data Archive.

### Oversight and Monitoring

#### Trial Steering Committee

Collectively, the trial steering committee includes expertise in geriatric mental health, chronic pain, qualitative and implementation research, and biostatistics, with particular expertise in JITAIs and MRTs. One or more members of the committee will meet with Wysa’s project leads at least biweekly on average.

